### Sample size calculation

Effect sizes will be calculated to describe treatment effects. We anticipate small effects (*d* = .24) concerning the primary outcome [4]. Based on a level of significance of *p* < .05, a statistical power of .80, one covariate, and two groups, *N* = 788 patients (394 in the control group and 394 in the intervention group) are necessary to detect a between-group effect (a priori power analysis of an ANCOVA with GPower version 3.1). With an expected participation rate of 32 % [34], we need to ask *N* = 2459 patients for study participation to reach this sample size. Considering that there were 4496 patients in the three cooperating clinics per year, we need to recruit patients for at least seven months to reach the planned sample size.

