**Methods/design:**

All patients who will be referred to inpatient psychosomatic rehabilitation in three clinics will receive a study flyer with information about how to log in to the study platform together with the usual clinic information leaflet. Patients will receive the study information and informed consent upon login and will be randomized into the intervention or the control group. The intervention group (*n* = 394) will get access to our virtual online clinic, containing several videos about inpatient rehabilitation, until their admission to inpatient rehabilitation. The control group (*n* = 394) will receive no special treatment preparation. Questionnaires will be given at study inclusion (T0), two weeks before admission to (T1), and at the end of (T2) inpatient rehabilitation. The primary outcome is the outcome expectancy measured with the Credibility Expectancy Questionnaire at T1. Secondary outcomes include treatment motivation, mental health, work ability, depression, anxiety, and satisfaction with and usage of the Internet platform.

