### Randomization

Participants will be assigned to the intervention and control groups using a stratified block randomization with a ratio of 1:1. Patients will be stratified based on the clinic they will be in during their inpatient rehabilitation. Randomization will be conducted with an algorithm implemented on the IP.

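### The stated d = .24, power .80 and N = 788 do not fit together: d = .24 needs 548, and 788 is the size for d = .20

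*Protocol article*

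**What the plan says.** The calculation is in the protocol article under Sample size calculation, and all its inputs are given there.

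- Effect size: "We anticipate small effects (*d* = .24) concerning the primary outcome [4" (a literature reference follows).
- Error rates and model: "Based on a level of significance of *p* < .05, a statistical power of .80, one covariate, and two groups".
- Result: a total of 788, stated as "394 in the control group and 394 in the intervention group) are necessary to detect a between-group effect".
- Tool: "a priori power analysis of an ANCOVA with GPower version 3.1".

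The same section then applies a 32% participation rate to reach 2459 patients to be approached, and sets this against 4496 patients per year to arrive at seven months of recruitment. It gives no allowance for loss between T0 and T1, no adjusted alpha and no correlation between baseline and outcome. The Randomization section specifies "stratified block randomization with a ratio of 1:1". The Statistical methods section names the T0 score of the Credibility Expectancy Questionnaire (CEQ) as the covariate and expects missing data, to be handled by multiple imputation.

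**The concern.** The article sets out a complete calculation, so it can be repeated, and the stated inputs do not return the stated N. This is the design basis for the primary outcome, CEQ outcome expectancy at T1. As written, a reader cannot tell whether the trial targets d = .20 or d = .24.

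Two things depend on the answer. The first is how a null result is read, because the effect the trial could have excluded differs between the two targets. The second is how much loss before T1 the design can bear: about 30% if the target is d = .24, and none if it is d = .20 at 80% power. The invitation count and the recruitment period also rest on this N.

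**Working it through.** **Inputs** (Sample size calculation and Randomization sections): d = .24; alpha .05, with sidedness not stated, but the ANCOVA F test is non-directional and so matches a two-sided test; power .80; two groups; one covariate; 1:1 allocation.

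**Formula.** For two equal groups f = d/2. Power comes from the noncentral F distribution with noncentrality λ = N·f², df1 = 1 and df2 = N − 2 − 1 = N − 3.

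**Attempt to reproduce 788 from the stated inputs.** f = .24/2 = .12. The smallest N reaching .80 is 547 (λ = 547 × .0144 = 7.88), or 548 in equal arms of 274. The normal approximation for two means gives 546. The stated figure is not reproduced: 788 − 548 = 240, and 240/548 = 44%.

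**What does give 788.** f = .10 (d = .20): the smallest N is 787 (λ = 787 × .01 = 7.87), or 788 in equal arms of 394. The ratio of the two requirements is what the effect sizes imply: (.24/.20)² = 1.44.

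**What 788 delivers if all provide T1 data:**

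| Quantity | Result |
|---|---|
| Power at d = .24 | .920 |
| Power at d = .20 | .801 |
| Detectable d at power .80 | .200 |

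**A second trace in the same section.** 787/.32 = 2459.4, which gives the stated 2459; 788/.32 = 2462.5, which does not. The number to be approached thus fits a program output of 787, the f = .10 result. The recruitment time follows from it: 2459/4496 × 12 = 6.6 months.

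**Other readings of the inputs, all at d = .24:**

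| Variant | N |
|---|---|
| One-sided alpha .05 | 430 |
| Power .85 / .90 / .95 | 626 / 732 / 905 |
| Alpha .025 / .01 | 663 / 815 |
| .24 entered as f | 139 |
| Covariate credited, r = .3 (N × (1 − r²)) | 547 × .91 = 498 |
| Covariate credited, r = .5 | 547 × .75 = 410 |

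None gives 788, and crediting the covariate moves N further away.

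**Effect of loss before T1.** The article gives no rate, so 10% and 20% are assumptions; the powers are for complete cases.

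- Target d = .20: 10% loss leaves 709 and power of about .76; 20% leaves 630 and about .71.
- Target d = .24: 20% loss leaves 630 and power of about .85; 30% leaves 552 and .804. The limit is 1 − 548/788 = 30.5%.

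**The case against.** The strongest defence is that 788 contains an unreported allowance for loss: 548/.695 = 788, so attrition of about 30% applied to the d = .24 requirement lands on the same N. This cannot be ruled out. But the text presents 788 as the direct result of the power program, the only later adjustment is for participation, and the defence leaves both the match to the d = .20 result and the 2459 as coincidences. Even if it were true, the section as written would still be wrong, because it says 788 are needed for the calculation itself.

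It can also be said that the error is harmless because it errs on the safe side. For d = .24 that stands: 788 exceeds the requirement, and the analysis model and its validity are untouched. It does not stand if d = .20 was the target, since there is then no margin for loss.

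Three stronger conclusions are tempting but not supported:

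- A reader might infer that d = .24 is simply a slip for .20. The arithmetic points that way, but this is inference; the article does not show whether the effect size, the power or N is the wrong element.
- A reader might infer that the trial has 92% power. That holds only at d = .24 and only if all 788 contribute T1 data.
- A reader might take the arm size in the abstract ("The control group (*n* = 394) will receive no special treatment preparation") as a second error. It gives a planned arm size with no effect size or power attached, and it remains correct if 788 is kept.

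**Conclusion.** The inconsistency is real and does not depend on any source outside the article. With alpha .05 and power .80 in the stated ANCOVA, d = .24 goes with 547 (548 balanced), and 787 (788 balanced) goes with d = .20. The stated N exceeds the one implied by the stated inputs by 240 patients. The result assumes a non-directional F test, equal arms and no variance credit for the covariate; relaxing the first or the third lowers N further below 788.

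The documents do not settle which figure is wrong, and they do not show that the trial is too small for d = .24. What needs correcting is the stated basis: the design target, and with it the margin for loss before T1, cannot be read from the section.

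**What to change.** Keep 788 randomized, state which effect size is the design target, and replace the basis with one of these:

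- (a) d = .20 (f = .10), power .80 with N = 788, assuming no loss before T1. Add that complete-case power falls to about .76 at an assumed 10% loss and .71 at an assumed 20%. Describing all 788 as evaluable at T1 would not do, because any loss would then require more than 788 randomized.
- (b) d = .24, power .92 if all 788 provide T1 data; 548 with T1 data suffice for .80, so 788 randomized tolerates about 30% loss.

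The cost is a change of wording in the Sample size calculation section. No further patients are needed under either statement, and the arm sizes in the abstract stay as they are.

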### Outcomes

The primary outcome in the study is the outcome expectancy (CEQ) measured at T1 (two weeks before admission to inpatient rehabilitation).

Key secondary outcomes are:Work-related therapy motivation (FBTM) at T1Treatment motivation (FREM-17 and PAREMO) at T1Treatment credibility (CEQ) at T1Satisfaction with and usage of IP at T1Mental condition (IRES-24) at T2 (end of rehabilitation)Satisfaction with inpatient rehabilitation (ZUF-8) at T2Subjective prognosis of work ability (SPE) at T2Depression and anxiety (PHQ-4) at T2Functioning in everyday life (IRES-24) at T2Perceived advantage of aftercare at T1 and T2

Predictors of outcome are:Therapy motivation (FREM-17 and PAREMO-20) at T0 (after randomization)Internet use and technology affinity at T0Use of websites with clinic reviews and ratings as well as use of the cooperating clinics’ websites at T1Previous, especially rehabilitation, treatments prior to the current inpatient rehabilitation at T0

We have defined four predictors of outcome which may have an additional impact on outcome, potentially confounding the impact of patients’ expectations. As it has a major influence on the therapy success, treatment motivation will be controlled [32]. We further think that strong Internet use and technology affinity may influence the use of our platform [33]. We will control for the use of websites with clinic reviews and ratings as well as the use of the cooperating clinics’ websites. Finally, we need to know if patients have had prior inpatient (rehabilitative) treatments, as previous experience may influence expectations. All predictors will be used as control variables in additional explorative analyses after testing our primary and secondary outcomes.

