### Statistical methods

Analysis of covariance will be used to evaluate the CEQ scores at T1 between the intervention and control groups with CEQ score at T0 as the covariate. The first eight secondary outcomes will be analyzed with analyses of covariance in analogy to the primary outcome. The last two secondary outcomes will be reported with descriptive statistics. Intention-to-treat analyses with multiple imputations to replace missing data as well as per-protocol analyses will be conducted.

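### The sample size is counted at randomization with no allowance for loss before the T1 primary outcome, and whether that costs power depends on an effect size that does not match N = 788

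*Protocol article*

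**What the plan says.** The Protocol article, Sample size calculation, sets out its planning chain in full. The effect: "We anticipate small effects (*d* = .24) concerning the primary outcome [4". The error rate: "Based on a level of significance of *p* < .05". The power and model: "a statistical power of .80, one covariate, and two groups". The result: "N* = 788 patients (394 in the control group and 394 in the intervention group) are necessary to detect a between-group effect", obtained by "a priori power analysis of an ANCOVA with GPower version 3.1". It then applies an expected participation rate of 32% and concludes that "we need to ask *N* = 2459 patients for study participation to reach this sample size". With 4496 patients a year in the three clinics, this becomes at least seven months of recruitment.

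Under Participants, patients are randomized once they consent online, and they receive the first questionnaire at once. Under Outcomes: "The primary outcome in the study is the outcome expectancy (CEQ) measured at T1", which is two weeks before admission. The Assessment section has T1 completed online. Under Statistical methods, the primary analysis is an ANCOVA of T1 CEQ with T0 CEQ as covariate, and the intention-to-treat analysis uses "multiple imputations to replace missing data".

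**The concern.** The ANCOVA draws its information from patients with a T1 score, but the planning chain ends at enrolment. The participation rate is applied to those asked to take part, so on its natural reading it covers consent and not later non-response. The plan itself expects missing values. Multiple imputation keeps every randomized patient in the analysis, but it does not in general restore the information in T1 scores that were never observed.

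If 788 is truly the number needed for .80 power, there is nothing to absorb T1 loss and the power claim is too high. If fewer are needed, the surplus is unexplained, because the article calls all 788 necessary. Either way, a reader cannot tell from the printed figures what power the primary analysis will have.

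**Working it through.** **Inputs from the article:** d = .24, alpha .05, power .80, two groups, one covariate, N = 788, participation 32%, 2459 invitations, 4496 patients per year. **Assumed here:** T1 loss of 10 to 40%, equal in both arms, because the article gives no rate. The test is taken as two-sided, because sidedness is not stated and the ANCOVA F test is two-sided in effect.

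**Step 1: does N = 788 follow?** Power comes from the noncentral F distribution with f = d/2, λ = N·f², df1 = 1 and df2 = N − 3. No variance reduction is credited to the covariate.

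- d = .24: f = .12. The smallest N with power .80 is 547 (λ = 547 × .0144 = 7.88), so 548 in equal arms. At N = 788, λ = 11.35 and power is .92.
- d = .20: f = .10. The smallest N is 787 (λ = 7.87), so 788 in equal arms, with power .80.
- Variants at d = .24 do not give 788: one-sided 430; power .90, 732; power .95, 905; alpha .025, 663; alpha .0125, 778; alpha .01, 815. Crediting a covariate correlation of .1 to .5 lowers N to between 542 and 411.

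Of the settings tried, only d = .20 reproduces 788.

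**Step 2: what is in the invitation figure?** 787/.32 = 2459.4, which is the printed 2459. The participation rate is the only factor applied. 2459/4496 × 12 = 6.6 months, consistent with the stated seven.

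**Step 3: power with 788 randomized and T1 loss.** Evaluable n = 788 × (1 − loss).

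| Assumed T1 loss | Evaluable n | Power, d = .24 | Power, d = .20 (r = 0) |
|---|---|---|---|
| 0% | 788 | .92 | .80 |
| 10% | 709 | .89 | .76 |
| 20% | 630 | .85 | .71 |
| 30% | 552 | .80 | .65 |
| 40% | 473 | .74 | .58 |

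At d = .24, the loss at which .80 is only just kept is 1 − 548/788 = 30.5%. The surplus is 788 − 548 = 240.

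**Step 4: credit for the T0 score at d = .20.** If d is in unadjusted SD units, the effective effect is d/√(1 − r²), where r is the T0–T1 correlation of the CEQ. The article gives no r.

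- r = .3: .20/√.91 = .210, N = 717, tolerable loss 1 − 717/788 = 9%.
- r = .5: .20/√.75 = .231, N = 591, tolerable loss 1 − 591/788 = 25%.

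**Step 5: is the recruitment plan large enough at the stated d?** From 547 evaluable, losses of 10/20/30% require 608/684/782 randomized and, at 32%, 1900/2138/2444 invited. All lie within 788 and 2459.

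**The case against.** The strongest reply is that the plan as written is safe. At its stated d = .24 it keeps power of at least .80 up to about 30% T1 loss, with no extra recruitment. The value d = .20 appears nowhere in the article; it is inferred because it reproduces 788. On this view the established error is the mismatch between d and N, and the missing loss rate is a follow-on.

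Most of this stands, and it rules out three readings that a reader might infer:

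- **That 788 patients must be evaluable at T1.** The article's wording suggests it, but its own d = .24 needs about 548.
- **That any T1 loss takes power below .80.** This needs d = .20 and also a T0 score that explains next to nothing, or a d already on the adjusted scale. At r = .5, a loss of about 25% could be absorbed.
- **That the invitation count is materially wrong.** 788/.32 is 2463 rather than 2459, but this is rounding from using 787. It changes recruitment time from 6.56 to 6.57 months and carries no weight.

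The reply does not show that the surplus at d = .24 is a planned reserve. The article describes no reserve and calls the whole 788 necessary. Nor can the gap be left to a fuller document, because the article prints the complete chain from effect size to months and its figures do not fit together.

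**Conclusion.** The concern holds in a limited form. The figures of 788 and 2459 refer to patients randomized and invited, and they contain no allowance for loss before the T1 primary outcome. They cannot stand as printed under either effect size: at d = .24, 788 is not the number needed, and at d = .20 with no covariate credit it leaves no margin.

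The document does not establish that the trial is underpowered. At an assumed 10 to 40% loss, power runs from .89 to .74 if d = .24, and from .76 to .58 if d = .20 with r = 0. These figures use evaluable patients only, so they take imputation to add little information, and they assume the 32% means enrolment. The source of that rate could not be checked.

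**What to change.** Keep 788 randomized and restate the figures.

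1. Decide whether d = .24 or d = .20 is the planning effect, and make N and d agree.
2. If d = .24 is kept, state that about 548 evaluable patients at T1 give .80 power and that the surplus of about 240 is the reserve for T1 loss of up to about 30%.
3. If d = .20 is the basis, state the assumed T1 loss with its source, the evaluable n and the lower power. If credit is taken for the T0 score, give the assumed correlation and say whether d is in unadjusted or adjusted SD units.
4. Check the overall T1 return rate early, blinded to arm, and update the stated power.

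The cost is a few sentences and possibly a less favourable power figure. No extra patients and no design change are required.

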### Randomization

Participants will be assigned to the intervention and control groups using a stratified block randomization with a ratio of 1:1. Patients will be stratified based on the clinic they will be in during their inpatient rehabilitation. Randomization will be conducted with an algorithm implemented on the IP.

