## Methods/design

### Participants

All patients referred to inpatient rehabilitation in one of the three cooperating clinics who are more than 18 years old are eligible for study participation. They will receive the study information together with the usual clinic documents and information about inpatient rehabilitation. Together with the study information, each patient will additionally receive a personal code and a link to the Internet platform (IP). After logging into the IP, patients need to agree to the informed consent presented on the platform. Patients who give their informed consent will be randomized to the intervention or control group and will receive the first questionnaire immediately.

Furthermore, all patients who complete all three questionnaires are eligible to take part in a drawing after completing the third assessment. Patients participating in the drawing can win one of ten cash checks worth 50 € each.

Personal data will be stored at the Study Center of Mental Disorders at the University Medical Center of the Johannes Gutenberg-University Mainz and each cooperating clinic. However, the study assistants with access to the personal data will have no access to the research data collected using questionnaires. Administration of the IP will be managed only by research fellows of the Department of Psychosomatic Medicine and Psychotherapy of the University Medical Center Mainz and the study assistants in the cooperating clinics.

The clinical protocol and informed consent were approved by the Ethics Committee of the Federal State of Rhineland-Palatinate (Germany), which is responsible for the coordinating center in Mainz (Ref. Number 837.192.15 (9960)). Additional approval from Ethics Committees responsible for the cooperating clinics is not necessary if the documents submitted by the coordinating center have been approved by an Ethics Committee. All procedures described in the clinical trial protocol (ClinicalTrials.gov identifier: NCT02532881) follow the International Conference on Harmonization-Good Clinical Practice (ICH-GCP) guidelines and the ethical principles described in the current revision of the Declaration of Helsinki. The trial will be carried out in accordance with local legal and regulatory requirements. A SPIRIT checklist is provided as an additional file (see Additional file 1).

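### Randomization is stratified by clinic, but the primary and analogous secondary ANCOVAs omit clinic, so reported standard errors are slightly too large

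*Protocol article*

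**What the plan says.** The Participants section of the protocol article defines the population as "All patients referred to inpatient rehabilitation in one of the three cooperating clinics". The Randomization section allocates patients "using a stratified block randomization with a ratio of 1:1" and adds: "Patients will be stratified based on the clinic they will be in during their inpatient rehabilitation". There are therefore three strata.

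The Statistical methods section compares CEQ at T1 "between the intervention and control groups with CEQ score at T0 as the covariate". It carries the same model to most secondary outcomes: "The first eight secondary outcomes will be analyzed with analyses of covariance in analogy to the primary outcome". The Sample size calculation section agrees with this model, since its inputs include "one covariate, and two groups".

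The Outcomes section lists four predictors for later exploratory adjustment: therapy motivation, Internet use and technology affinity, use of clinic and review websites, and previous treatment. Clinic is not among them and is named in no other analysis.

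**The concern.** Blocking within clinic balances the arms in each clinic, so differences between clinics hardly contribute to the arm difference. A model without clinic does not use this. It counts between-clinic variation as residual noise and reports a standard error larger than the true sampling variability of the estimate. Confidence intervals are then somewhat too wide, the test runs below its nominal 5% level, and some power is given away.

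This is more than a detail left for the analysis plan. The article names the covariate, sizes the trial on one covariate and extends the model to eight secondary outcomes. A later plan that added clinic would depart from the published model.

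**Working it through.** **Inputs from the protocol article.** N = 788 (394 per arm), 1:1 allocation in blocks within three clinics, d = .24, alpha .05 (taken as two-sided, as for an ANCOVA F test), power .80, one covariate, two groups.

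**Inputs not in the article.** R2 is the share of the T1 CEQ variance left after T0 CEQ that clinic explains. No value is given, so 0 to .10 is assumed. The effect size is taken in units of the residual SD after T0 CEQ.

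**Step 1: the plan's own figure.** The power comes from a noncentral F distribution with 1 and N-2-1 degrees of freedom, noncentrality N × f² and f = d/2.
- With d = .24 (f = .12), the required N is 547, not 788.
- With d = .20 (f = .10), the required N is 787, or 788 with equal arms.
- At N = 788, power is 92.0% for d = .24 and 80.1% for d = .20.

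The stated 788 therefore matches d = .20. That mismatch is a separate matter. Here it means only that both effect sizes should be shown.

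**Step 2: standard errors.** The residual variance after T0 CEQ is set to 1.
- Reported without clinic: SE_rep ≈ sqrt(4/788) = .0713.
- True under balance within clinic: SE_true = sqrt((1-R2) × 4/788).
- Ratio: SE_rep/SE_true = 1/sqrt(1-R2).

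**Step 3: test level and power (normal approximation).**
- Type I error without clinic = 2 × Φ(-1.96 × SE_rep/SE_true).
- Power without clinic = Φ((d - 1.96 × SE_rep)/SE_true).
- Power with clinic = Φ(d/SE_true - 1.96).

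Example at R2 = .10: SE_true = .0713 × sqrt(.90) = .0676, and the ratio is 1.054. Type I error is 2 × Φ(-1.96 × 1.054) = .039. For d = .24, power is Φ((.24 - .1397)/.0676) = 93.1% without clinic and Φ(.24/.0676 - 1.96) = 94.4% with it.

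| R2 (assumed) | Reported SE too large by | Type I error without clinic | Power at d = .24, without / with | Power at d = .20, without / with |
|---|---|---|---|---|
| 0 | 0% | .050 | 92.1% / 92.1% | 80.2% / 80.2% |
| .01 | 0.5% | .049 | 92.2% / 92.3% | 80.3% / 80.5% |
| .05 | 2.6% | .044 | 92.6% / 93.3% | 80.8% / 82.1% |
| .10 | 5.4% | .039 | 93.1% / 94.4% | 81.4% / 84.1% |

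In terms of interval width, a model with clinic gives the same width with 788 × (1-R2) patients: 749 at R2 = .05 and 709 at R2 = .10.

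**Step 4: simulation check.** 4000 trials per setting, three clinics of 264, 264 and 260 patients, blocks of four (an assumption).
- Type I error without / with clinic: .049 / .050, .043 / .051 and .039 / .048 at R2 = .01, .05 and .10.
- Power at d = .20 without / with clinic: 79.8% / 80.0%, 82.0% / 83.2% and 80.6% / 83.2%.
- At R2 = .10 and no effect, the mean reported SE without clinic was .0713 against an empirical SD of .0680. With clinic the figures were .0676 and .0680.

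The Monte Carlo error of a simulated power near .80 is sqrt(.8 × .2/4000) ≈ .006. Single values therefore scatter around the closed form, and the closed-form table is the better guide.

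**The case against.** The strongest objection is that residual clinic variance in the primary outcome is probably small. CEQ at T1 is collected two weeks before admission, so nobody has yet been treated in a clinic. The clinic is already known at randomization, and T0 follows randomization, so clinic differences in expectancy should largely sit in the T0 score. This stands: values of .05 and .10 are likely high for this outcome, and at .01 the effect is negligible.

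The gain also depends on the effect size and its scale. At the stated d = .24 it is at most about one point of power over the range shown. If d were in raw SD units and the T0-T1 correlation were .6 (an assumption), the residual SD would be .8, d would become .24/.8 = .30 in residual units, and power would be about 99% with or without clinic. This stands too.

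A reader might infer more than the article supports:
- **That the primary result would be biased or its type I error inflated.** It would not. The estimate keeps the benefit of balance within clinic, and the error is in the conservative direction.
- **That T2 outcomes must suffer a larger loss.** It is possible, since they follow treatment in different clinics. Satisfaction with inpatient rehabilitation (ZUF-8) is scheduled only at T2 in Table 1, so no baseline score can absorb a clinic effect. But the article gives no figure for it.
- **That the imputation model is itself defective.** The article names only the method, and its content is commonly left to the analysis plan.
- **That the one-covariate count in the sample size calculation is a second error.** It only confirms how the model is meant.

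**Conclusion.** The point holds as a minor one. The article fixes a stratified design and an analysis model that omits the stratification factor. Over the assumed range of R2 from 0 to .10, the reported standard error is 0% to 5.4% too large and the test level lies between .050 and .039. The power given up is 0 to 1.3 points at d = .24 and 0 to 2.7 points at d = .20. These figures rest on an assumed clinic effect, on effect sizes in residual-SD units and on close balance within clinic. The omission does not invalidate the primary conclusion. It is worth correcting because the correction aligns the reported precision with the design at almost no cost.

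**What to change.** Add clinic as a fixed three-level factor to the primary ANCOVA, next to T0 CEQ, and to the secondary ANCOVAs run on the same pattern. As a consequence, the imputation model should contain the same terms as the analysis model. The cost is one clause of text and two of the 785 residual degrees of freedom (788-2-1). The sample size need not change on this account. Stating the term in advance also prevents a choice between models with and without clinic after the data are seen.
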